**Methods:**

We will conduct a two-arm, parallel randomised controlled trial involving children and adolescents (8–11 and 12–17 years of age, respectively) with symptoms of anxiety, depression or both, according to the 25-item Revised Child Anxiety and Depression Scale (*t*-score > 70). A total of 280 participants will be randomised to the intervention group or the active control group, in a 1:1 ratio. Those in the intervention group will receive five weekly sessions of cognitive-behavioural therapy via teleconference. The sessions will focus on stress responses, family communication, diaphragmatic breathing, emotions, anger management, behavioural activation and cognitive restructuring. Participants in both groups will have access to 15 videos covering the same topics. Participant-guardian pairs will be expected to attend the sessions (intervention group), watch the videos (control group) or both (intervention group only). A blinded assessor will collect data on symptoms of anxiety, depression and irritability, at baseline, at the end of the intervention and 30 days thereafter. Adolescents with access to a smartphone will also be invited to participate in an ecological momentary assessment of emotional problems in the week before and the week after the intervention, as well as in passive data collection from existing smartphone sensors throughout the study.

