
The first four sessions all have a homework component, encouraging the family to practice the strategies between sessions. Each session starts by reviewing the previous week’s homework. As the focus of the intervention is on skills building, the child/adolescent and the main guardian (preferably a parent) will both be required to participate in all sessions. It is expected that parent/guardian participation will improve learning because the adult should act as a model for the child/adolescent on how (and when) to employ the techniques learned. Some of the interventions are also focused on teaching the guardians new skills (such as establishing better routines at home and listening empathically to their child).

The intervention also comprises 15 psychoeducational videos that revise and deepen the content of the sessions. Families are expected (and encouraged) to watch the videos between sessions. The topics of each video are as follows:• Video 1—general information regarding the project and psychoeducation on stress responses• Video 2—parenting, communication and cooperation between family members• Video 3—diaphragmatic breathing• Video 4—a version of the diaphragmatic breathing video adapted for children• Video 5—progressive muscle relaxation• Video 6—mindfulness• Video 7—psychoeducation on emotions• Video 8—fear, sadness and anxiety• Video 9—coping with irritability• Video 10—behavioural activation• Video 11—establishing routines• Video 12—use of electronics by children and adolescents• Video 13—sleep hygiene• Video 14—cognitive restructuring• Video 15—coping with an anxiety attack

Each video is approximately 5 min in length. The families will have access to them via the COMVC smartphone application [40], which is available for Android and iOS. Videos will be made available according to the following schedule: first week, videos 1 to 6; second week, videos 7 to 9; third week, videos 10 to 13; and fourth week, videos 14 and 15.

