#### Active control group

Children and adolescents in the active control group will receive a psychoeducational intervention that consists of the same 15 videos described above. The videos will be made available through the same smartphone application and on to the same schedule described for the intervention group.

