### Criteria for discontinuing or modifying allocated interventions {11b}

Patients requiring a more intense type of treatment, such as individual psychotherapy or psychotropic medication, because of an increase in symptomatology (e.g. emergence of suicidal ideation), will be referred to the appropriate facility.

If a participant in the intervention group misses a session, the team will attempt to reschedule it, respecting the following criteria: no more than 4 weeks should elapse between the first and last session, and there should be at least 48 h between sessions, in order to allow families enough time to carry out the proposed homework. The fifth session can also be used to cover any topic that was missed because of participant inability to attend a previous session.

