### Outcomes {12}

The primary outcome measure will be a change in the symptoms of anxiety and depression, as determined by the RCADS-25-P and RCADS-25-C [28, 29], between study entry (T0) and 1–3 days after the end of the intervention (T1, after five sessions of psychotherapy, five weeks of access to the psychoeducational videos, or both). The RCADS-25-P and RCADS-25-C will be completed by an independent clinician blinded to the allocation, on the basis of interviews (through videoconference or telephone call) with the guardians and the children/adolescents, respectively. The response variables will be the continuous T-scores for the three RCADS-25 domains (total, depression and anxiety).

Secondary outcomes will include the following: a change in the symptoms of anxiety and depression at follow-up; global functioning, assessed by the Clinical Global Impression (CGI) scale [41] and the Children’s Global Assessment Scale (CGAS) [30, 42]; the impact of mental health symptomatology, as determined with the Strengths and Difficulties Questionnaire (SDQ) impact supplement [43]; changes in irritability; emotional problems; environmental changes, as determined by passive smartphone data collection; the level of parental satisfaction with the telepsychotherapy sessions; and the potential harm (emergence of suicidal ideation and worsening of the quality of family relationships).

The blinded assessor will evaluate the difference between the anxiety and depressive symptomatology observed at T0 and that observed at follow-up (T2, 30 days after the last psychotherapy session, for the intervention group, or 30 days after the last video is made available, for the active control group) in an interview with the guardian and the child/adolescent, using the RCADS-25-P and RCADS-25-C.

The blinded assessor will evaluate the global functioning of the participants in interviews with the guardian and the child/adolescent (through videoconference or telephone call). The CGI-Severity (CGI-S) and CGAS scores obtained at T0 will be compared with those obtained at T1 and with those obtained at T2. Scores on the CGI-S range from 1 to 7, higher scores corresponding to greater symptom intensity. Scores on the CGAS range from 0 to 100, higher scores indicating better functionality. The CGI-Improvement (CGI-I) scores will be assessed at T1 and T2. Scores on the CGI-I range from 1 (“very much improved”) to 7 (“very much worse”).

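### T2 is anchored to different events in the two arms, and the control anchor precedes the end of the control intervention, so control follow-up is about 2 to 3 weeks after T1, not the stated 30 days after the intervention

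*Protocol article*

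**What the plan says.** The abstract (Methods) gives one schedule for both groups: assessment "at baseline, at the end of the intervention and 30 days thereafter".

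Outcomes {12} is more detailed. T1, the primary time point, is "1–3 days after the end of the intervention (T1, after five sessions of psychotherapy, five weeks of access to the psychoeducational videos, or both". T2 has a separate rule in each arm: "30 days after the last psychotherapy session, for the intervention group, or 30 days after the last video is made available". The second rule is the one that applies to controls.

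The video timetable is under Intervention description {11a}. The later releases are "third week, videos 10 to 13; and fourth week, videos 14 and 15". For controls, the section Active control group adds: "The videos will be made available through the same smartphone application and on to the same schedule described for the intervention group". The last release is therefore in week 4 in both arms.

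The sessions are five and weekly. Section {11b} limits rescheduling: "no more than 4 weeks should elapse between the first and last session".

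**The concern.** Three statements about the control arm do not fit together. Its intervention lasts five weeks, its follow-up clock starts in week 4, and its follow-up is described as 30 days after the intervention. The intervention arm's clock starts at a different kind of event, the last session.

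Two things are at stake. First, T2 may fall at different elapsed times in the two arms, and the interval from T1 to T2 differs between them. Any general change in symptoms over time would then be mixed with the arm difference in the secondary follow-up outcomes. Second, Outcomes {12} compares suicidal ideation at T1 with T2, using an instrument that looks back two weeks. Unequal T1–T2 intervals mean that a different share of the follow-up period is observed in each arm.

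**Working it through.** **Inputs**
- Five weekly sessions: days 0, 7, 14, 21 and 28 ({11a}). Day 28 is also the limit of the 4-week cap ({11b}).
- Last videos released in week 4: day 21 at the earliest, day 27 at the latest ({11a}).
- Control intervention: five weeks of access, ending on day 35 (Outcomes {12}).
- T1: end of intervention plus 1 to 3 days. T2: anchor plus 30 days (Outcomes {12}).
- Assumption: day 0 is both session 1 and the first video release. The article gives no common start date.

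**The stated 30 days, intervention arm.** T2 = 28 + 30 = day 58. If the intervention ends with session 5, T2 is 58 − 28 = 30 days later, so the abstract's figure is reproduced.

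**The stated 30 days, control arm.**
- T1 = 35 + 1 to 35 + 3 = day 36 to 38.
- T2 = 21 + 30 to 27 + 30 = day 51 to 57.
- T2 after the end of access = 51 − 35 to 57 − 35 = 16 to 22 days. The 30 days are not reproduced.
- T1 to T2 = 51 − 38 to 57 − 36 = 13 to 21 days.

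**Intervention T1, two readings.** The T1 rule is "after five sessions of psychotherapy, five weeks of access to the psychoeducational videos, or both". The intervention arm receives both components, so T1 may follow session 5 or may wait for the fifth week of access.

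| | T1 (day) | T2 (day) | T1 to T2 (days) | T2 after end of intervention (days) |
|---|---|---|---|---|
| Control | 36–38 | 51–57 | 13–21 | 16–22 |
| Intervention, T1 after session 5 | 29–31 | 58 | 27–29 | 30 |
| Intervention, T1 after five weeks of access | 36–38 | 58 | 20–22 | 23 |

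**Difference between arms.** At T2: 58 − 57 to 58 − 51 = 1 to 7 days, controls earlier. At T1: 36 − 29 = 7 days, controls later, under the first reading; nil under the second.

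**Recall windows for suicidal ideation.** The T2 interview covers the preceding 14 days. In controls, a gap of 13 days overlaps T1 by 1 day, and a gap of 21 days leaves 21 − 14 = 7 days unobserved. In the intervention arm, 27 − 14 to 29 − 14 = 13 to 15 days are unobserved under the first reading, and 20 − 14 to 22 − 14 = 6 to 8 days under the second.

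**Sensitivity.** If the last session falls on day 21, intervention T2 is day 51: level with the earliest control T2 and 57 − 51 = 6 days before the latest. If control access is taken to end on day 28, contrary to Outcomes {12}, control T1 is day 29 to 31, T1 to T2 is 51 − 31 to 57 − 29 = 20 to 28 days, and T2 is 23 to 29 days after the end. That is still short of 30.

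**The case against.** The strongest reply is that this concerns a secondary visit. The primary outcome is the change from T0 to T1, for which Outcomes {12} gives a single rule. Only the intervention arm receives both sessions and videos, so the last alternative in that rule naturally describes that arm. T1 is then day 36 to 38 in both arms. This stands: a reader might infer that the primary comparison is misaligned, but the documents support that under one of two readings only.

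A reader might also infer that controls are always followed up earlier and that this favours the intervention. That needs a common day 0 and session 5 on day 28. Sessions may be rescheduled with as little as 48 hours between them, and the first four take priority if time runs out ({18b}), so the T2 order can be equalised or reversed. No direction of bias can be claimed, and no size either: the documents give no rate at which scores drift over these weeks.

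A third inference is that a child who stops after session 1 would have T2 on day 30. Section {18b} weakens this. It requires both assessments however many sessions were completed, and it frames its 4-week limit in terms of scheduled sessions. The T2 definition does not itself say whether the last session is the attended or the scheduled one, but the scheduled reading is the more sensible.

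Finally, time enters the model as a continuous variable (Statistical methods {20a}), and the abstract is only a summary. Whether actual dates are used may properly be left to an analysis plan that is not shown. If they are, the model could absorb part of the timing difference in the scores, but it would not equalise the recall windows. Nor does the conflict rest on the abstract alone: within Outcomes {12}, the control T2 clock starts before the five-week control period is over.

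**Conclusion.** The T2 rule is wrong as written. On the protocol's own timetable, control T2 falls 16 to 22 days after the control intervention ends and 13 to 21 days after T1, not the 30 days stated. These two control-arm results do not depend on how intervention T1 is read or on a shared start date. They need only release in week 4 and five weeks of access.

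The between-arm results are conditional. With a common start and weekly sessions, the arms are assessed 1 to 7 days apart at T2. The intervention T1–T2 interval is 27 to 29 or 20 to 22 days, against 13 to 21 in controls. The consequences fall on the secondary follow-up outcomes and on the comparison of suicidal ideation between T1 and T2. The primary comparison is out of step, by about 7 days, only if intervention T1 follows session 5 without waiting for the fifth week of access. The direction and size of any bias remain open.

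**What to change.** Define T1 and T2 in both arms as the same number of days from one common origin, such as randomisation or release of video 1. Use one visit window and apply it regardless of how many sessions were attended. Reconcile the abstract, the video timetable in {11a} and Outcomes {12} with that definition.

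As an illustration, placing T2 30 days after the five-week period in both arms, with T1 after week 5 in both, puts T2 on day 35 + 30 = 65 and makes T1 to T2 65 − 38 to 65 − 36 = 27 to 29 days in each arm.

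Recruitment began in October 2021 (Trial status), so some children may already have been assessed under the current rule. For them, use the actual assessment day as the time variable or in a sensitivity analysis.

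The cost is an amendment to the visit definition and the scheduling rule. No visits are added. Some intervention children would be seen a few days later after their last session: in the illustration, (65 − 28) − 30 = 7 days later at T2.

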Participants ≥ 12 years of age with access to a smartphone will be asked to install an application designed to passively collect data from the smartphone sensors—the passive remote measurement technology (pRMT) application from the Remote Assessment of Disease and Relapse (RADAR)-base platform [47]. The pRMT application will run in the background, requiring minimal input from participants, and will use the smartphone sensors to collect data on the following: ambient noise and light; relative GPS location (i.e. the distance travelled, rather than absolute coordinates or precise geographical location); the number of Bluetooth-enabled devices nearby; the duration of calls; the number of text messages and emails; the time spent using the smartphone; the time spent on social media; and battery life. Passive data collection will take place from T0 to T2. The aim of these measures is to determine whether parameters such as physical activity (estimated by the distance travelled) and proximity to other people (estimated by analysing Bluetooth connectivity with other smartphones) might be related to changes in anxiety and depressive symptomatology and whether those parameters show any improvement after the trial.

To assess the level of parental satisfaction with the telepsychotherapy sessions (intervention group only), parents will be asked to complete an adapted version of the Telemedicine Satisfaction Questionnaire (TSQ) [48].

Potential harms were defined as the emergence of suicidal ideation and worsening of the quality of family relationships. As previously mentioned, we will use the parent-report four-item MFQ-SI to assess suicidal ideation in the last 2 weeks [31, 32], comparing T1 with T2. The MFQ-SI will be completed by the blinded assessor in an interview with the guardian (through videoconference or telephone call). To identify worsening of the quality of family relationships in the last 2 weeks, we will use the family relationship subscale of the family impact module of the Pediatric Quality of Life Inventory (PedsQL) [49]. The PedsQL will be completed by the blinded assessor in interviews with the guardian at T0, T1 and T2. The family relationship subscale of the PedsQL comprises five items, covering topics such as “lack of communication between people in my family”. For each item, there is a 5-point Likert scale (responses ranging from “never” to “almost always”).

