## Data collection and management

### Plans for assessment and collection of outcomes {18a}

All assessors will be clinical psychologists with previous experience in child and adolescent mental health who have been trained in the study protocol by the study team coordinators. The instruments used in the assessments are described below.Sociodemographic questionnaire—the guardian will complete an online form designed to collect data on socioeconomic status, level of education, occupation and income, as well as data such as the age/sex of the child/adolescent, COVID-19 exposure history and routines (including study hours, sleep habits, sleep quality and screen time). Sleep quality will be assessed with an adapted version of the Single-item Sleep Quality Scale, which is comparable to other sleep scales such as the Pittsburgh Sleep Quality Index [56]. Guardians will rate the sleep quality of their child/adolescent according to a 5-point Likert scale ranging from 0 (“terrible”) to 4 (“excellent”).DASS-21 [50]—The DASS-21 is a 21-item scale covering internalising symptoms in depression, anxiety and stress domains over the last 2 weeks. It consists of 21 statements (e.g. “I found it hard to wind down”) that will be scored by the guardians using a 4-point Likert scale ranging from 0 (“did not apply to me at all”) to 3 (“applied to me very much or most of the time”). It has been shown to possess adequate validity and reliability in the Brazilian population (Cronbach’s alpha: 0.92 for the depression subscale; 0.90 for the stress subscale; and 0.86 for the anxiety subscale) [57].RCADS-25—The RCADS-25 is a shortened version of the Revised Child Anxiety and Depression Scale. The original scale has 47 items and has been shown to be appropriate for use in various cultures, including that of Brazil [58]. The 25-item version is comparable to the original scale, and its use is preferred to reduce the burden of the respondent [30]. As previously mentioned, we will apply the RCADS-25-P and RCADS-25-C [28, 29]. In a clinical sample, the alpha coefficients for the RCADS-25-C depression and anxiety scales were 0.80 and 0.91, respectively, whereas they were 0.79 and 0.76, respectively, in a community sample [29]. For the RCADS-25-P, the reported alpha coefficients were 0.83 for the depression scale, 0.85 for the anxiety scale and 0.85 for the total scale [28].MFQ-SI [31, 32]—The original MFQ is a 33-item questionnaire on mood symptomatology that has been adapted for use in Brazil [59]. Guardians will answer only the questions on the four-item composite version related to suicidal ideation (MFQ-SI), a topic that is not covered on the RCADS-25.PedsQL—The PedsQL family impact module is a 36-item parent-report questionnaire that aims to assess the impact of chronic medical conditions on the quality of life of the family [49]. It has been adapted for use in Brazil [60]. We will use its five-item family relationships subscale to assess family dynamics. The subscale employs a 5-point Likert scale with responses ranging from “never” to “almost always” on topics such as “lack of communication between people in my family”.SDQ—The original SDQ is a 25-item questionnaire on child and adolescent psychopathology that has been adapted to many languages and used extensively in various countries, including Brazil [43], in its informant-report and self-report forms. There is an extended version of the SDQ [61] that includes a brief impact supplement (comprising five questions) designed to assess the potential burden related to the psychopathology of a child in areas such as home life and academic performance. For this study, we will use only the SDQ impact supplement, in order to assess the burden of the depressive and anxiety symptomatology.ARI—The ARI is a seven-item irritability scale that includes six items related to symptoms related to irritability and one item related to the potential impact of irritability [62]. The ARI has been adapted for use in Brazil [45].TSQ [48]—Parental satisfaction with the telepsychotherapy sessions will be assessed (in the intervention group only) with an adapted version of the TSQ [48]. It is a 14-item questionnaire that assesses parameters such as difficulties in contacting the therapist and willingness to use telemedicine services again.EMA of emotional problems—We will deliver an ESM protocol to assess mood, stress and emotion (Table 1). The protocol will be delivered using the COMVC application, which will send notifications for participants to rate affirmations about their current state (e.g. “Right now, I feel happy”) using an 8-point Likert scale with responses ranging from “not at all” to “very much”. It represents a brief version of the ESM protocol used in the Remote Assessment of Disease and Relapse in Major Depressive Disorder study [47], a prospective multicenter study to determine the usability, acceptability and feasibility of remote collection of data regarding the symptoms of depression.pRMT—The pRMT application, from the RADAR-base platform [47], will be used in order to monitor the following smartphone features: the position sensor, which allows the relative location to be registered by using data on latitude and longitude; the movement sensors (accelerometer, gyroscope and magnetometer), which allow movement to be registered by measuring acceleration, rotation and the raw magnetic field, as well as by counting steps; environmental (light) sensors, which register the level ambient light; and activity logs, which include the time spent using the smartphone in general and on specific applications, as well as battery level and nearby Bluetooth-enabled devices.

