## Discussion

Videoconferencing in mental health was first employed approximately 70 years ago, in the 1950s [27], and its use increased considerably during the COVID-19 pandemic [64]. However, despite the growing body of literature on the topic, there is still a scarcity of scientifically validated protocols focusing on telepsychotherapy for children and adolescents [27]. If proven effective, the present protocol could not only help increase the evidence in this area but also represent a tool to improve access to mental health care even outside the context of the pandemic. The intervention is described in detail in the manual, which should facilitate its reproduction in other contexts. It is based on cognitive-behavioural techniques, some of which have previously been tested in crisis situations [65]. We have adapted some of those strategies to take advantage of new technologies, such as the delivery of psychoeducational videos via the internet.

One aspect of our study that is secondary but still of great relevance is the use of the smartphone as a tool to collect participant data, which is expected to increase ecological validity and reduce memory bias [66]. The use of passive data collection by the pRMT application might allow us to draw interesting correlations between mental health symptomatology and aspects such as screen time and physical activity.

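### Physical activity is to be estimated from GPS distance with no stated transport filter, although another section says the same application counts steps

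*Protocol article*

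**What the plan says.** Outcomes {12} describes passive data collection by the pRMT application, from T0 to T2, in participants aged 12 or over who have a smartphone. Its list of collected data includes "relative GPS location (i.e. the distance travelled, rather than absolute coordinates or precise geographical location" and names no movement sensor and no step count. The same section gives the purpose: to see whether parameters, with "physical activity (estimated by the distance travelled" as one example, "might be related to changes in anxiety and depressive symptomatology and whether those parameters show any improvement after the trial".

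Plans for assessment and collection of outcomes {18a} describes the same application: "The pRMT application, from the RADAR-base platform [47], will be used in order to monitor the following smartphone features". Its list includes "the movement sensors (accelerometer, gyroscope and magnetometer), which allow movement to be registered by measuring acceleration, rotation and the raw magnetic field". Step counts are named there too.

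The Discussion returns to the theme and hopes for "correlations between mental health symptomatology and aspects such as screen time and physical activity".

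No section shown says that steps or acceleration will be used to estimate physical activity, and none says that they will not.

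**The concern.** The protocol names a construct, physical activity, and also names the quantity that will stand for it. Deriving a variable in detail can be left to an analysis plan. Here the choice of proxy is already written into the protocol, so it can be judged as it stands.

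GPS distance differs from physical activity in two ways. It rises with travel by car or bus, which involves little activity, and it hardly moves with exercise done in one place. An adolescent who goes back to school by bus would appear more active, while one who takes up exercise at home would appear much the same.

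The stake is a mislabelled secondary finding. The topic also has some link to the trial's reasoning: the Background cites more sedentary behaviour during the pandemic, and session 3 is devoted to behavioural activation. If distance changes alongside symptoms, readers will be told something about physical activity when the signal may be about travel.

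**Working it through.** The protocol gives no figure for this variable, so there is none to reproduce. The check has two parts.

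**1. The two descriptions of the pRMT data, side by side**

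| Item | Outcomes {12} | {18a} |
|---|---|---|
| Relative location from GPS | yes | yes |
| Accelerometer, gyroscope, magnetometer | not listed | yes |
| Step count | not listed | yes |
| Ambient noise | yes | not listed |
| Calls, text messages, emails | yes | not listed |
| Light, Bluetooth devices, phone use, battery | yes | yes |

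Neither list contains the other, so the text alone does not settle which is complete. The physical activity parameter is tied to the one movement-related item in the {12} list, distance. The items closer to bodily movement appear only in {18a}.

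**2. How much of GPS distance could be walking**

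The documents give no walking distance, commuting distance or mode of travel. The inputs below are assumptions:

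- walking, w: 2 to 4 km a day on 7 days
- motorised round trip, m: 10 to 20 km on 5 school days

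Weekly distance = 7w + 5m. Walking share = 7w / (7w + 5m).

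| w (km/day) | m (km/school day) | Walking (km/week) | Motorised (km/week) | Walking share |
|---|---|---|---|---|
| 2 | 20 | 14 | 100 | 14/114 = 12% |
| 2 | 10 | 14 | 50 | 14/64 = 22% |
| 4 | 20 | 28 | 100 | 28/128 = 22% |
| 4 | 10 | 28 | 50 | 28/78 = 36% |

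Doubling the walking adds 7w to the total, so the weekly distance rises by the same 12-36%. Missing one motorised trip removes m from the total: 10/78 = 13% at the low end and 20/114 = 18% at the high end. Under these assumptions, one missed school trip can move the weekly figure by more than a doubling of walking does (18% against 12% in the first row), or by less (13% against 36% in the last).

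An adolescent with no motorised commute would show little of this distortion. Exercise in one place adds almost nothing to distance under any inputs.

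**3. Which analyses are touched**

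- *Between arms.* The arms are randomised concurrently, so travel habits and changes in pandemic mobility should balance on average. Unrelated travel mainly adds variance. A difference in distance would still be a valid randomised comparison of distance, but its name would be wrong.
- *Correlation with symptom change, and before/after.* Randomisation does not help here. Recruitment ran from October 2021 with an expected end in January 2023. A return to school or outings in that period could raise distance and could itself accompany symptom change.
- *Primary outcome, sample size, error rates.* None uses this variable.

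**The case against.** The strongest reply is that this is a preference about a minor measure. Physical activity is not itself a listed outcome: {12} lists environmental changes from passive data and then offers physical activity as an example parameter. Participation in passive data collection is optional under Confidentiality {27}, the Discussion speaks only of possible correlations, and {20a} attaches no specific test to this variable. The wording also says estimated, which admits an imperfect proxy. Feature derivation, speed filters and recording thresholds are commonly left to documents not shown. Most of this stands, and it limits the point to a low-priority improvement. It does not remove the point, because the protocol itself names the proxy and a closer one appears in its own sensor description.

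Several stronger readings are tempting but unsupported:

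- *That GPS distance is dominated by motorised travel.* This depends wholly on assumed travel habits. The documents contain no such data.
- *That physical activity cannot be derived from distance at all.* A noisy proxy still carries some information.
- *That steps measure activity directly.* A phone counts steps only while it is carried, and it is often put down for sport, dance or exercise at home. Step count would miss some of the same activity.
- *That the plan discards the step data.* {18a} lists step counting among the features to be monitored, and nothing says it will be left out of the analysis.
- *That steps are certainly recorded.* That relies on {18a} over {12}, and the two lists disagree.

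**Conclusion.** The point holds in a limited form. As written, physical activity is estimated by GPS distance with no stated transport or speed filter, so vehicle travel counts as activity and stationary activity is largely missed. Section {18a} describes closer signals from the same application that the data list in {12} omits.

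The size is uncertain. The range of 12-36% for the walking share rests on the assumed 2-4 km walked daily and 10-20 km motorised on five school days. It is an illustration, not an estimate for this population. The mismatch between measure and construct does not depend on those numbers.

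The reach is small: an optional, exploratory secondary measure in participants aged 12 or over, chiefly its correlation with symptom change and its before/after reading. It is worth correcting because the correction is nearly free, but it does not bear on the trial's main conclusion.

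**What to change.** 1. Reconcile the lists of pRMT data in {12} and {18a}, so that both name the same sensors.
2. If steps and acceleration are recorded, as {18a} states, estimate physical activity by daily step count, supported by accelerometer data. Report GPS distance separately and call it mobility.
3. If they are not recorded, keep the GPS measure but call it mobility in {12}, and drop the claim to physical activity there and in the Discussion.

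What counts as a day with enough recording can be left to the analysis plan.

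In the second case the cost is wording only, with no new data collection, participant burden or change in sample size. In the third case the trial gives up a statement about physical activity that the GPS measure could support only weakly. The one drawback of step count is that steps are missed when the phone is not carried, a limit that GPS distance shares.
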